##### Choice of outcome measure

Inferences of potentially suitable outcome measures will be based on results from descriptive pre–post analysis of outcome measures, and qualitative analysis of interviews and feedback from free-text responses from patients, carers and staff participants regarding reported impact of the intervention.

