**Ethics and dissemination:**

The study is approved by the University College London Research Ethics Committee (reference: 15281/002). The findings will be shared through peer-reviewed scientific journals and conferences, and traditional, online and social media platforms.

Strengths and limitations of this studyThe Let It Out intervention has been developed based on evidence from a scoping review of previous research, and refined drawing on insights from testing it in a slightly different form in another population and feedback from key stakeholders.The acceptability and feasibility of the intervention will be explored using a rich, mixed-methods approach, using process evaluation to triangulate quantitative recruitment, retention and acceptability data with qualitative written and interview feedback.Recruitment may be restricted by the relatively short recruitment period and potential limitations on hospice staff capacity (due to COVID-19 related pressures on hospice teams).The study is taking place during a time of transition and ongoing change in methods of care, necessitated by the evolving COVID-19 pandemic that may restrict generalisability of the findings outside of this context.This is a single-arm study not designed to formally evaluate efficacy of the intervention.

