## Methods and analysis

### Design

A pragmatic, single-arm, multisite, mixed-methods longitudinal study. The study design has been developed in line with the latest Medical Research Council (MRC) guidelines,^32 33^ which recommend an iterative intervention development and evaluation process. Mixed-methods, pragmatic study designs are recognised as an appropriate way for researchers to approach the development and evaluation of complex interventions in palliative care.^34^ We are employing a convergent design to integrate quantitative measures of fidelity, feasibility, acceptability and possible impact, with semi-structured interviews and focus groups. In the qualitative aspect of the study, we will take a phenomenological approach to capture more nuanced feedback on the participants’ experience of the intervention, including their views on its design, acceptability and any perceived effects.^34 35^ The quantitative and qualitative data will be integrated through a process evaluation. As the focus of the study is on applying pragmatic mixed-methods to optimise intervention design, this study will not formally evaluate nor test *a priori* hypotheses regarding its efficacy or report p-values.

The study is approved by the University College London Research Ethics Committee (reference: 15281/002).

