### Participants

The study will be conducted in three population groups recruited from participating hospices:

#### Group 1

Up to 40 adults living with terminal illness receiving palliative care from a UK hospice (on an inpatient, day care, outpatient or community basis). A sample size of 40 is recognised by the National Institute of Health Research as being appropriate for intervention feasibility and pilot work that is not designed to evaluate efficacy.^36 37^

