##### Impact on psychological and physical well-being

Inductive thematic analysis of interviews and feedback from free-text responses from patients, carer and staff participants. DM will develop codes from the raw data, to be checked and adjusted by the research team; data will be re-coded, checked and adjusted until code saturation is reached.Descriptive pre–post analysis of changes in outcome measures (Integrated Palliative Care Outcome Scale, Patient Health Questionnaire 9, Generalised Anxiety Disorder 7, Sleep Quality Scale, uptake on mental health services): mean and standard deviation of scores at each time point.Descriptive summary of number of adverse effects reported by clinical team and participants.

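### The stated basis for choosing future outcome measures is uncontrolled pre–post results and reported impact, so chance, decline or attrition could favour or discard a measure

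*Protocol article*

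**What the plan says.** Informing the choice of outcome measures for a possible larger evaluation is a listed secondary objective (Aims and objectives). The section Choice of outcome measure gives its analysis in one sentence. The quantitative basis is: "Inferences of potentially suitable outcome measures will be based on results from descriptive pre–post analysis of outcome measures". The qualitative basis is: "qualitative analysis of interviews and feedback from free-text responses from patients, carers and staff participants regarding reported impact of the intervention".

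The section Impact on psychological and physical well-being defines the quantitative part. It plans "Descriptive pre–post analysis of changes in outcome measures" for four scored scales (IPOS, PHQ-9, GAD-7, Sleep Quality Scale) and for mental health service uptake, reported as "mean and standard deviation of scores at each time point". It mentions neither a comparator nor a restriction to people measured at both times.

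The Design section describes "A pragmatic, single-arm, multisite, mixed-methods longitudinal study". The Participants section sets Group 1 at up to 40, on the ground that "A sample size of 40 is recognised by the National Institute of Health Research as being appropriate for intervention feasibility and pilot work" not designed to evaluate efficacy. The strengths and limitations list says: "This is a single-arm study not designed to formally evaluate efficacy of the intervention".

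Table 1 is broader than the Choice of outcome measure section. It assigns outcome measure selection to the health questionnaires, the post-session ratings, the feedback form and the interviews, and the interviews cover participants' experience of the questionnaires as well as of the intervention.

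**The concern.** Both stated bases concern apparent effect: how far scores moved, and what impact people reported. Whether a scale suits a future trial depends largely on other things: whether very ill people complete it, whether they skip items, whether scores pile up at one end, how variable they are, and whether respondents find the questions relevant and bearable.

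Without a control arm, movement in a scale cannot be attributed to the intervention. Patients are excluded if they are not expected to live beyond 10 weeks. The 2-week intervention and 8-week follow-up together take about 10 weeks. Some decline and loss within the measurement window is therefore plausible, although the article gives no expected rate. A scale could look promising because sicker patients stopped answering, or look useless because decline hid a benefit. A future trial could then inherit a poorly founded primary outcome.

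**Working it through.** There is no planned figure to reproduce: the sample size of 40 rests on a feasibility convention, with no effect size, SD or precision target. The checks ask how large a spurious change could be.

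**Inputs from the article.** Up to 40 patients; 4 scored scales; follow-up immediately and 1, 4 and 8 weeks after the final session (abstract and Table 1), giving 4 × 4 = 16 cells. The section Self-report measures—group 1 lists only 1, 4 and 8 weeks, giving 4 × 3 = 12 cells, so both counts are shown.

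**Assumptions.** All correlations, dropout rates and drifts below are assumed; the article gives none.

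**1. Chance.** Suppose no true change, correlation 0.5 between scales and 0.6 between follow-ups. Each mean change has standard error 1/√n in SDs of change. By simulation the expected maximum of 16 such standardised means is 1.325 standard errors, and of 12 it is 1.217.

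| n | 1/√n | Best of 16: 1.325/√n | P(some cell > 0.3 SD), 16 cells | Best of 12: 1.217/√n |
|---|---|---|---|---|
| 40 | 0.158 | 0.21 | about 22% | 0.19 |
| 30 | 0.183 | 0.24 | about 33% | 0.22 |
| 20 | 0.224 | 0.30 | about 49% | 0.27 |

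For sensitivity, use baseline-SD units with SD of change √(2(1−ρ)), pre–post correlation ρ from 0.5 to 0.7, correlation between scales 0.3 to 0.6 and between follow-ups 0.5. The best of 16 then averages 0.16 to 0.24 SD at n = 40 and 0.23 to 0.34 SD at n = 20.

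The 95% half-width for one mean change, with no picking of a maximum, is 1.96 × √(2(1−ρ))/√n. At n = 40 it is 0.31 (ρ = 0.5) to 0.24 (ρ = 0.7); at n = 20 it is 0.44 to 0.34.

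**2. Attrition.** Suppose nobody changes, a fraction d drops out, and dropout correlates r with a worse score. The mean among those remaining looks better by r × φ(z)/(1−d), where z is the normal quantile at 1−d.
- d = 0.2: φ(0.842)/0.8 = 0.280/0.8 = 0.350, so the shift is 0.105 SD (r = 0.3) to 0.175 SD (r = 0.5).
- d = 0.4: φ(0.253)/0.6 = 0.386/0.6 = 0.644, so the shift is 0.193 to 0.322 SD.

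Means taken over whoever answered at each time point carry this shift. Paired change in the same respondents removes it in this no-change case.

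**3. Disease course.** Suppose scale A truly gains 0.3 SD from the intervention and scale B 0.1 SD, with pre–post correlation 0.6 and correlation 0.4 between the two changes. The standard error of the difference in observed change at n = 40 is √(2 × 0.4)/√40 × √(2 × 0.6) = 0.155. If A also worsens naturally by w, the chance that A shows the larger change is Φ((0.3 − w − 0.1)/0.155):
- w = 0: Φ(1.29) = 90%
- w = 0.2: Φ(0) = 50%
- w = 0.3: Φ(−0.65) = 26%

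Each mechanism alone can create or hide a change about as large as the gains assumed in step 3.

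**The case against.** The strongest reply is that the article contains no rule of the kind simulated in step 1. A reader might infer that the scale that moved most will be chosen. The text does not support that: it speaks tentatively of inferences about potentially suitable measures, and gives no ranking, threshold or single winner. This stands, and it makes step 1 an illustration of what leaning on change can do.

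A reader might also infer a contradiction with the disclaimer on efficacy. That does not hold either. The Design section says that "this study will not formally evaluate nor test" a priori hypotheses about efficacy, and exploring possible impact descriptively is an openly listed objective. Nor does the article say that a future effect size will be taken from these data.

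It would also be too strong to call uncontrolled change uninformative. In step 3, with no drift, it identifies the more responsive scale 90% of the time. It is weak and confounded evidence.

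Some of the better evidence is already planned. SDs are part of the pre–post analysis, completion at each time point is reported under Feasibility and acceptability, and Table 1 links the feedback form and the interviews to outcome selection. A condensed article may also leave item-level missingness and floor or ceiling tables to a fuller document, so their absence alone is no fault.

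What remains is the basis that the article does state. It rests on apparent effect, confines the qualitative input to reported impact, and is narrower than Table 1.

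**Conclusion.** The point holds as a weakness in a stated method. The Choice of outcome measure section rests its inferences on uncontrolled change and perceived impact without naming measurement properties, and the planned summaries are not restricted to the same respondents. This risks favouring or discarding a measure for reasons other than its responsiveness to the intervention.

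The spurious best-cell change is about 0.21 SD at n = 40 and 0.30 SD at n = 20 with four follow-ups, or 0.19 and 0.27 SD with three. Attrition and natural decline can add to or mask this. All these sizes depend on the assumed values, and the best-cell figures apply only if someone looks for the largest change. No sample size or primary analysis is affected. It is a cheap improvement.

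**What to change.** Rewrite the Choice of outcome measure section so that suitability is judged mainly on:
- completion of each instrument at each time point, and missing items;
- the share of participants at floor and ceiling at baseline;
- the SD and the baseline–follow-up correlation;
- views of relevance and burden from the interviews and feedback form that Table 1 already links to this objective.

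Report pre–post change as paired change among the same respondents, beside the number lost at each time point, as supporting information only. Change need not be ignored, but state that its size or direction will not by itself decide the choice of measure or set the effect size for a future trial.

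The cost is one paragraph and a few more descriptive tables from data already collected. No new data, participants or procedures are needed.

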##### Potential underlying mechanisms

Responses to expression session prompts will be analysed quantitatively using LIWC software^51^ and triangulated with indicators of intervention impact on well-being to inform development of a preliminary theoretical model.

##### Core concerns on referral to hospice

Responses to expression session prompts will be analysed using inductive thematic analysis. DM will develop codes from the raw data, to be checked and adjusted by the research team; data will be re-coded, checked and adjusted until code saturation is reached.

### PPI

The funding application for this programme of work was reviewed by [name], a Marie Curie PPI representative. [name] is also a member of the advisory group overseeing the conduct of the PhD studentship of which this study is a part. [name], along with a second PPI representative ([name]) have reviewed the study and intervention design. [name] and [name] will be consulted at key stages of the research. Furthermore, the study as a whole has been designed based on the principles of co-design; the data from participants will be used to inform the design of the final intervention and potential future research.

### Data management

All survey-based data (demographics and health-related questionnaires) will be collected using REDCap^47 48^ via University College London Data Safe Haven. The Data Safe Haven has been certified to the ISO27001 information security standard and conforms to National Health Service Digital’s Information Governance Toolkit. Built using a walled garden approach, the data is stored, processed and managed within the security of the system, avoiding the complexity of assured endpoint encryption. A file transfer mechanism enables information to be transferred into the walled garden simply and securely. A data management plan has been registered and approved by the University College London Data Protection Office outlining methods to maintain participant privacy and data integrity and confidentiality. At the end of the project, anonymised data will be uploaded to open-access data repository ReShare.^55^

### Ethics and dissemination

#### Confidentiality

All participant data will be collected via the secure REDCap via Data Safe Haven platform,^47 48^ or Microsoft Teams (interviews/focus groups), except audio-recordings or photographs of expression sessions, which will be sent directly to a dedicated study telephone via WhatsApp secured by end-to-end encryption. The phone will be carried by a member of the research team or stored in a locked drawer. Only members of the research team will have access to participant data. Consent and data collection forms will be securely stored in the University College London Data Safe Haven. During analysis, data will be pseudonymised using a unique ID that could not be linked to a participant’s identity by anyone outside of the research team. Data will be anonymised 3 months after participants’ involvement in the study ends.

### Serious adverse events

Any serious adverse events (SAEs) attributed to a person’s participation in the study will be recorded on the online study platform, and in the participant’s medical records. SAE forms will be provided by the chief investigator to the sponsor within 5 days of becoming aware of the event.

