### Aims and objectives

The primary objective of the study is to optimise the design of an ED-based intervention (LIO) tailored for people receiving palliative care from a UK hospice. The secondary objectives are to:

Assess whether the intervention and study procedures are acceptable and feasible in UK hospice services.Explore the potential impact of the intervention on psychological and physical well-being, and identify any potential adverse effects.Inform the choice of outcome measures and study design for possible future large-scale intervention evaluation.Explore the causal mechanisms underlying potential intervention efficacy.

An exploratory objective is to explore the core concerns of people following referral to hospice care. This is one of the topics covered in the intervention expression sessions; responses could potentially inform strategies to minimise or address those concerns.

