### Data collection

#### Overview—group 1

Table 1 provides a detailed description of the participant timeline and outcome measures for Group 1 participants.

**Table 1 T1:** Group 1 participant timeline, outcome measures and analysis approach

Measure	Time points administered	Description	Data type	Analysis approach	Relevant research objective*
Demographics	Baseline	Approximate date of hospice referral, age, gender, ethnicity, marital status, religious background, level of education, type of care (eg, inpatient, outpatient, day care), diagnosis, mental health history and COVID-19 status.	Quantitative	Descriptive statistics	1. Feasibility and acceptability
Expression sessions	Three sessions over 2-week intervention period	Typed, handwritten or audio-recorded responses to three expression sessions that make up the LIO intervention.	Quantitative and qualitative	LIWC and BIR inductive thematic analysis (session 2)	Feasibility and acceptability Underlying mechanisms Exploratory objective (session 2)
Health-related outcome measures (see below for details)	Baseline, immediately after the final expression, and, 1 week, 4 weeks and 8 weeks after the final expression	See below for details.	Quantitative	Descriptive statistics and descriptive pre–post analysis	Feasibility and acceptability Impact on well-being Outcome measure selection Underlying mechanisms
Integrated Palliative Care Outcome Scale (IPOS)—patient version^56^		An updated, brief (10 questions, 17 items) version of the POS instrument. IPOS was developed specifically to capture a range of the most important concerns of people living with palliative-stage disease, covering symptoms, information needs, practical concerns, anxiety or low mood, family anxieties and overall feeling of being at peace. Items in question 2–9 are scored from 0 to 4, and overall scores can range from 0 to 68. Questions 1 and 10 are not scored.			
Patient Health Questionnaire 9^57^		A 9-item instrument developed to screen for major depressive disorder, and validated in palliative care populations.^58^ Items are scored 0 to 3, and it can be scored continuously or with validated cut-offs for mild (5 to 9), moderate (10 to 14), moderately severe (15 to 19) and severe depression (20 to 27).^59 60^ The cut-off for a depression ‘case’ is 10.			

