*The research team will have a dedicated study phone that a member of the research team keeps only on their person during working hours (09:00–17:00 Monday–Friday) and is kept in a secure locked cabinet outside of those hours. The phone will be checked once a day for recordings or photos received, at which point the recording will be transferred to the dedicated project file on Data Safe Haven and deleted from the phone.

#### Self-report measures—group 1

All self-report data is collected online using the Research Electronic Data Capture (REDCap) online survey platform.^47 48^ Group 1 participants will complete a demographics questionnaire at baseline (prior to receiving the intervention). They will also complete a series of health-related questionnaires at baseline and 1, 4 and 8 weeks after the final intervention session (secondary outcome measures). Group 1 participants will also be prompted to log in to the platform during or after each expression session to indicate they have completed the session, and (if they wish) to share their response with the research team. Directly after each expression session they will also be prompted to complete a short self-report questionnaire to monitor their mood, and perception of how meaningful and personal the session was (secondary outcome measures). After the final expression session, participants will also complete a feedback form (primary outcome measure).

#### Semi-structured individual interviews (primary outcome measure)—group 1

Semi-structured interviews (n≤15) will be conducted within 8 weeks of the participant’s final expression session. Interviews will be conducted by DM, following a topic guide to explore participants’ experience of the intervention and questionnaires, including whether they experienced any negative feelings during or after each expression, whether they found the intervention helpful and the appropriateness and relatability of the expression session prompts, expanding on the topics covered in the feedback form.

Interviews will take place virtually and will be audio-recorded using Microsoft Teams, to minimise face-to-face interactions in line with government COVID-19 guidance. Recordings will be transcribed verbatim for analysis; transcripts will be pseudonymised and personally identifiable information redacted from the transcript.

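### Serious events are logged only once attributed to the study, and PHQ-9 and GAD-7 are summarised only by mean and SD, so the counting of harm is weakly served

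*Protocol article*

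**What the plan says.** One of the secondary objectives in the protocol article (Aims and objectives) is: "Explore the potential impact of the intervention on psychological and physical well-being, and identify any potential adverse effects". Two places set out how harm is to be counted.

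- **Serious adverse events:** "Any serious adverse events (SAEs) attributed to a person’s participation in the study will be recorded on the online study platform", and also in the medical records. The section gives no rule for serious events not so attributed. It does not say who judges attribution or by what criteria.
- **Impact on psychological and physical well-being:** the harm summary is a "Descriptive summary of number of adverse effects reported by clinical team and participants". The pre–post analysis of the health measures is specified as "mean and standard deviation of scores at each time point".

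Table 1 says of the PHQ-9 that "it can be scored continuously or with validated cut-offs for mild (5 to 9), moderate (10 to 14") and so on upward. It gives similar bands for the GAD-7 and a case cut-off of 10 for both. The stated analysis does not use these bands or the cut-off.

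The article also asks about harm actively. There is a mood rating after every session, and a researcher contacts each participant at the end of weeks 1 and 2. There is a feedback form after the last session. The patient interview covers experience of the sessions, "including whether they experienced any negative feelings during or after each expression". Carer and staff topic guides include risk of harm.

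**The concern.** Serious events, including some deaths, are to be expected in this population over roughly 10 weeks (2 weeks of intervention and 8 of follow-up). With no control arm, the only way to ask later whether a run of events looks unusual is to have all of them on file with a judgement beside each. A rule that judges first and records second removes that possibility. A reader of the report could not tell whether few serious events means few occurred or few were attributed.

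The score summary raises a similar problem. A mean and SD per time point describe the group among those who responded. They do not follow a person from baseline, so a minority who deteriorate can be offset by small gains in the rest. The question is a live one here, because the article (The intervention, Development) says feedback from the forerunner study led to changes meant to limit short-term distress.

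**Working it through.** The article gives no calculation on harm to reproduce, and the sample size of up to 40 rests on a convention. The check is therefore a reading of the rules plus two illustrations. All event rates, score changes and the baseline SD below are assumed, because the documents give none.

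**Step 1. What each source can deliver.**

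| Source | Who is covered | What it gives | What it does not give |
|---|---|---|---|
| SAE rule | all of Group 1 | serious events already attributed | total serious events; later re-judgement |
| Count of reported adverse effects | all of Group 1 | a number, with no attribution condition stated | within-person score change |
| Mean and SD of PHQ-9, GAD-7 | responders at each time point | group level and spread | who worsened, and how many |
| Session mood rating | all who complete sessions | feeling just after each session | change up to 8 weeks |
| Well-being contacts | each participant, end of weeks 1 and 2 | active check during the intervention | follow-up period; the article does not say they feed the count |
| Patient interviews | at most 15 of 40 = 37.5% | direct question on negative feelings | a count over all participants |

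No row gives a total count of serious events, and none gives individual deterioration on the validated scales.

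**Step 2. Effect of attribution before recording.** With n = 40, true event rate p per participant, and a share q of events attributed (and so recorded), the chance of recording at least one event is 1 − (1 − pq)^40. At p = 5%:

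- q = 1: 1 − 0.95^40 = 0.87
- q = 0.5: 1 − 0.975^40 = 0.64
- q = 0.25: 1 − 0.9875^40 = 0.40

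**Step 3. What the mean hides.** Suppose 4 of 40 worsen by 8 PHQ-9 points and 36 improve by 1.

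- Mean change: (4×8 − 36×1)/40 = (32 − 36)/40 = −0.1, an apparent slight improvement.
- Share clearly worse: 4/40 = 10%.

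**Step 4. Whether the SD reveals it.** In the same example, the variance of the change is (4×64 + 36×1)/40 − 0.1² = 7.3 − 0.01 = 7.29. If the baseline SD is 5 and change is unrelated to baseline, the follow-up SD is √(25 + 7.29) = 5.7. A rise from 5 to 5.7 does not show how many worsened, or by how much.

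**Step 5. What a count would show.** If those 4 also moved up a band, the table would read 4/40 = 10%, exact (Clopper–Pearson) 95% CI 2.8% to 23.7%. That is imprecise, but it is visible.

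**The case against.** The strongest reply is that the plan looks for harm in several ways that do not pass through the SAE rule. This stands. A reader might infer that harms are captured only if already attributed or volunteered unprompted. The article does not support that. The attribution condition is stated for serious events only, the count of adverse effects carries no such condition, and mood ratings, well-being contacts and interviews all ask. The first two of these are well placed to pick up short-term distress.

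A reader might also infer that those who developed the intervention judge attribution, or that other deaths go unrecorded altogether. The article does not say who attributes. It also tracks retention separately through recruitment and data-collection records, where deaths may well appear.

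It can be said that shift tables are detail for a fuller plan, and that the mean-and-SD phrase is shorthand, since its list also includes service uptake, a yes/no item. This stands in part. A fuller document may say more, but the article does not merely leave the analysis open: after naming pre–post change, it specifies a summary per time point.

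Finally, with progressive illness and no control arm, moving up a band cannot be separated from disease course. That is correct. It limits how the table may be read, but it is no reason to leave the table out.

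**Conclusion.** The point holds in a limited form. As written, the plan yields no total count of serious adverse events and no view of individual worsening on PHQ-9 or GAD-7, although the bands and the cut-off of 10 are set out in Table 1. The aim to "identify any potential adverse effects" is not defeated. It is exploratory, and the qualitative and mood data can identify candidates. What is weakly served is its quantitative part.

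The size of the problem cannot be read from the documents. The fall from 0.87 to 0.64 assumes a 5% event rate with half of events attributed, and the mean change of −0.1 rests on invented scores. Both show the mechanism only. It would be wrong to cite the upper confidence limit for zero events in 40 as evidence of the flaw: that limit depends on n alone and would be the same under a better recording rule.

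This is an inexpensive improvement to reporting and does not undermine the study's primary purpose of optimising the intervention.

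**What to change.** 1. **Recording.** Reword the SAE section so that every death and serious adverse event the team learns of is recorded, with relatedness to participation as a separate field. Report the total and the number judged related.
2. **Analysis.** Under the impact analysis, add one table for PHQ-9 and GAD-7. At each follow-up it should give the number responding, and the number and percentage (with 95% CI) who moved up a severity band or crossed from below 10 at baseline to 10 or above. Label it as uncontrolled change, not as an effect of the intervention. It needs no p-values, so it fits the stated design.

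**Cost.** One field on the SAE form, some extra log entries for at most 40 people, and one table from data already collected, with no added burden on participants. The drawback is that many logged events and some band shifts will reflect disease course, which the report should say.
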